#### Concealment mechanism {16b}

This is not applicable, because the parents or caregivers of the children will probably know which drugs their children receive during the SMC campaign.

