### Participant timeline {13}

#### Sample size {14}

Haemoglobin (Hb) concentration was used to calculate the sample size. Given that the mean Hb concentration in the SMC alone group in a previous study [18] in the same population was 10.5 g/dl, we assumed a mean Hb concentration of 11.0 g/dl in the SMC + anthelminth arm and a SD of the Hb concentration of 1.5 g/dl. To detect a mean difference between the treatment arms of 0.5 g/dl with 90% power at a 95% level of statistical significance, a minimum of 189 children per treatment arm will be needed. Allowing for 10% loss to follow-up, approximately 200 children will be enrolled into each treatment arm.

Based on a recent survey conducted in the study site (unpublished data), we assumed that the prevalence of any malaria or helminth infection in the SMC group will be 30%, the prevalence of any malaria or helminth infection in the SMC + anthelminth arms will be 16% and the relative risk will be 0.53 (that is, 47% reduction in the SMC + anthelminth arms compared to the SMC alone group). A minimum sample size of 188 children was considered sufficient to give 90% power at 95% confidence interval and 5% level of precision. Adding 10% loss to follow-up, approximately 200 children will be needed for each treatment arm. Therefore, a total of 600 children aged 1–14 years will be enrolled and randomly assigned at a ratio of 1:1:1 into the control and the two intervention arms.

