### Assignment of interventions: allocation

#### Sequence generation {16a}

Randomisation will be used to minimise bias in the assignment of eligible children to the study arms to increase the likelihood that known and unknown attributes (e.g. demographic and baseline characteristics) are evenly balanced across arms and to enhance the validity of possible statistical comparisons across arms. Randomisation will be performed by a study pharmacist in blocks of 3 using a table of random numbers and will be stratified by age groups.

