#### Implementation {16c}

The allocation sequence will be generated by a study pharmacist. The study participants will be enrolled by trained research assistants who will assign the participants to the treatment arms.

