#### Procedure for unblinding if needed {17b}

The design is open label with only outcome assessors being blinded, so unblinding will not occur.

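### Allocation concealment is declined for a reason that belongs to blinding, and fixed blocks of three make assignments predictable to any recruiter who can follow the sequence

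*Protocol article*

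**What the plan says.** All references are to the protocol article.

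- **Concealment mechanism {16b}**, in full: "This is not applicable, because the parents or caregivers of the children will probably know which drugs their children receive during the SMC campaign". No envelopes, central service or pharmacy-held release are described.
- **Sequence generation {16a}**: "Randomisation will be performed by a study pharmacist in blocks of 3 using a table of random numbers and will be stratified by age groups". The number of age strata is not given, nor whether villages or assistants had separate lists.
- **Implementation {16c}**: "The allocation sequence will be generated by a study pharmacist". Then: "The study participants will be enrolled by trained research assistants who will assign the participants to the treatment arms".
- **Procedure for unblinding {17b}**: "The design is open label with only outcome assessors being blinded, so unblinding will not occur".
- **Sample size {14}**, on the 600 planned enrolments: "children aged 1–14 years will be enrolled and randomly assigned at a ratio of 1:1:1 into the control and the two intervention arms".

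The timing also matters. Recruitment {15} places consent one day before the start. Table 2 places the questionnaire, baseline samples, randomisation and the first study drugs on Day 0. Section {18a} has staff check again on the start day that the parent is still willing. The exclusion criteria leave acute illness to be judged when the drugs are given. Trial status reports recruitment complete on 21 June 2022.

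**The concern.** Concealment and blinding protect different things. Concealment acts before assignment: whoever decides that a child enters must not know which arm comes next. Blinding acts afterwards. Item 16b answers the first question with a reason that bears only on the second. Because the item is answered and declined, this is a wrong stated rule and not a detail left to a fuller document.

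With concealment declined, the block design matters more. When the block size equals the number of arms, each block contains every arm exactly once, so earlier assignments reveal later ones. The person who could use that information is the one enrolling.

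The primary outcome is adverse events over six days, which a child's health at entry can affect. The trial is framed as non-inferiority on safety, so keeping frailer children out of the anthelminthic arms would favour the conclusion being sought. The tests named under Statistical methods {20a} for prevalence, anaemia and haemoglobin (Hb) are unadjusted chi-square and t-tests. Repeated-measures analysis of variance brings in baseline values for parasite counts and Hb only. The comparisons therefore rest largely on the balance that randomisation is meant to give.

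**Working it through.** The article gives no predictability figure to reproduce. The check is a direct count.

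**Inputs.** Three arms at 1:1:1 and 600 children (Sample size {14}); block size 3 (Sequence generation {16a}). That makes 600 / 3 = 200 blocks, each one of the 3! = 6 orderings of the arms.

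**Assumption.** The recruiter knows the block size and sees the earlier assignments in the same block and age stratum.

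**Chance of guessing the next arm, by position in the block**

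| Position | Arms still possible | Probability correct |
|---|---|---|
| 1 | 3 | 1/3 |
| 2 | 2 | 1/2 |
| 3 | 1 | 1 |

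- Mean: (1/3 + 1/2 + 1) / 3 = 11/18 = 61.1%, or 600 × 11/18 ≈ 367 correct.
- By chance: 1/3 = 33.3%, or 200 correct.
- Known with certainty: one per block, 200 of 600.

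**Incomplete last blocks.** Each stratum can end with at most two children in an unfinished block. With S strata the number of certain assignments is then at least (600 − 2S) / 3. That is 198 for S = 3 and 196 for S = 6, so the effect is small.

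**If the assumption holds only in part.** Let f be the share of blocks that a recruiter can follow in full, with guessing at chance elsewhere. The correct share is 1/3 + f × (11/18 − 6/18) = 1/3 + f × 5/18, and the certain count is 200 × f.

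| f | Guessed correctly | Certain |
|---|---|---|
| 0 | 33.3% | 0 |
| 0.5 | 47.2% | 100 |
| 1 | 61.1% | 200 |

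If the list itself can be read, the known share rises towards 100%.

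**Would other blocks have solved it?** The fixed sizes are enumerated exactly. The varied sizes are simulated, with a guesser who knows the candidate sizes and all earlier assignments.

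| Blocks | Certain | Guessed correctly |
|---|---|---|
| Fixed 3 (as planned) | 33.3% | 61.1% |
| Fixed 6 | 20.0% | 56.1% |
| Fixed 9 | 14.3% | 53.2% |
| Varied 3/6/9 | about 4% | about 56% |
| Varied 6/9/12 | about 2.5% | about 53% |

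Varying the blocks removes most of the certainty but little of the guessing advantage. Concealed release is the essential part.

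**Is there still room to select?** Consent precedes randomisation, so the pool of children is largely formed before assignment. Two decisions stay open on Day 0: the parent's renewed agreement and the judgement of acute illness. Table 2 lists baseline sampling and randomisation on the same day and does not say that baseline data are recorded before the arm is known.

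**The case against.** The strongest objection is that the one-in-three figure is conditional. A pharmacist, not a recruiter, generates the sequence. Stratification by age runs several block series at once. Recruitment was scheduled to start on 17 June 2022 and was complete on 21 June, with several assistants visiting homes across villages. If they drew on shared lists, none of them need have seen a whole block. If each had a separate list, following it would be easy, since an assistant who assigns knows the arms already given. The article does not say which applied, and calling the design open label does not settle who saw past assignments. This stands. A reader might infer that at least a third of assignments were known in advance, or that recruiters worked from an open list. The text supports neither.

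Second, there are partial safeguards. Age stratification restrains imbalance between age groups, acutely ill children are excluded, and consent comes before randomisation. These narrow the routes for selection. They do not close them, because steering within a stratum and the two Day 0 decisions remain.

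Third, 61% measures opportunity, not bias. This also stands: no distortion of adverse events or Hb has been estimated, and baseline samples taken before dosing allow imbalance to be looked for. Blinded safety assessors protect measurement of the outcome. They have no bearing on who entered each arm.

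**Conclusion.** The point holds in conditional form. Item 16b is wrong as written: it declines concealment for a reason that concerns blinding. Fixed blocks of 3, and the same staff enrolling and assigning, increase the exposure.

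For a recruiter who knows the block size and sees earlier assignments in the stratum, about 200 of 600 assignments are certain and about 61% can be guessed, against 33% by chance. Without that knowledge the advantage shrinks towards nothing; with sight of the list it approaches complete foreknowledge. The article neither states nor prevents either situation.

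A reader might go further and conclude that selection took place, or that the safety and efficacy comparisons are invalid. The document gives no evidence for that. What it shows is an unprotected step that must be reported and checked before the comparisons are read as fully randomised.

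**What to change.** **For the children already enrolled**

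1. Replace the statement in {16b} with an account of what was done: who held the list, whether lists were shared or separate, when each arm was revealed relative to eligibility, consent and baseline sampling, and whether assistants knew the block size. Amend {16c} to match.
2. Report baseline Hb, age and infection by arm. If enrolment order was recorded, also report them by position in block. The most telling comparison is between arms among third-position children, whose arm could have been known.
3. Add a selection-bias sensitivity analysis (for example a Berger–Exner analysis, which needs enrolment order) or a comparison adjusted for baseline age, Hb and infection, covering the adverse-event outcome as well. Adjustment deals only with measured differences.

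The cost is some wording, a table and one further analysis. The baseline measurements are already in the plan. The article does not say whether enrolment order or block position was kept, so that part may not be possible.

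**For any further enrolment**

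Release each allocation only after eligibility, consent and baseline data are recorded. It can be held by the pharmacist, held centrally, or kept in sequentially numbered opaque sealed envelopes. Separate enrolment from assignment, and use larger or randomly varied undisclosed blocks as an addition to concealed release, not a substitute for it. The cost is modest set-up. The article describes its REDCap server for data only, so a randomisation function there should not be assumed.

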#### Implementation {16c}

The allocation sequence will be generated by a study pharmacist. The study participants will be enrolled by trained research assistants who will assign the participants to the treatment arms.

### Assignment of interventions: blinding

#### Who will be blinded {17a}

To minimise bias, the study staff who will administer the drugs to the children will be a completely separate group of staff from those who will conduct safety assessment for the study participants. This group of study staff who will perform the safety assessments will be blinded to the treatment arms. The data analyst will not be masked to the sources of the data.

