### Outcomes {12}

#### Primary outcome

All solicited and unsolicited adverse events will be assessed for causal relationships to the study medications, for six consecutive days after the administration of anthelminthic drugs.

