#### Methods in analysis to handle protocol non-adherence and any statistical methods to handle missing data {20c}

The intention-to-treat (ITT) method will be used to analyse data obtained from all study participants assigned to a group by randomisation. Data from study participants who complete all four cycles of SMC will be analysed using per protocol method. Participants who have only a pre- or post-intervention data will be excluded from the full analysis set.

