A passive surveillance system will also be implemented during the subsequent SMC cycles to complement the system described above. All study participants presenting for admission through the outpatient or emergency departments of Saraya health centre and health posts in the study villages will be evaluated. During the hospitalisation, the participant’s course of illness will be monitored to capture the symptoms and signs indicative of a severe adverse event. A blood sample for the evaluation of malaria parasites will be taken for all children attending a clinic who are reported to have had a fever within 24 h of presentation or have a measured axillary temperature of ≥37.5°C. Other possible sources of fever will also be investigated. A malaria rapid diagnosis test (RDT) will be performed to guide immediate patient management.

The investigators will evaluate any safety information that is spontaneously reported by a study participant beyond the time frame specified in the protocol. The investigators will monitor and analyse the study data including all adverse events and clinical laboratory data as they become available and will make determinations regarding the severity of the adverse events and their relation to a study drug. The investigator or clinical designee will review both adverse drug reactions and other adverse events to ensure prompt and complete identification of all events that require expedited reporting as serious adverse events.

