The global trend towards integrated, non-disease-specific approaches to controlling co-endemic diseases such as malaria and helminths has become an increasingly recognised strategy, but limited information exists on the safety, feasibility and effectiveness of combining SMC with helminth control at the community level [36, 37]. SMC involves administration of full treatment courses of antimalarial medications at monthly intervals during the malaria transmission to prevent malaria illness, with the objective of maintaining the therapeutic anti-malaria drug concentrations in the blood throughout the period of greatest malaria risk [31]. The approved preventive chemotherapy for mass drug administration (MDA) for STH and schistosomes (albendazole [ALB] and praziquantel [PZQ]) respectively, and the SMC drugs (AQ plus SP) work well with minimal side effects when used separately [35, 38]. Given that 4-aminoquinoline drugs are reported to have antagonistic pharmacokinetic interactions with praziquantel [39], the SMC partner drugs, AQ (a 4-aminoquinoline derivative) and SP will not be administered at the same time with anthelminthic drugs (albendazole and praziquantel) in this study. Because albendazole and praziquantel have a short half-life of 8.5 h and <2h respectively [22], anthelminthic drugs (praziquantel and albendazole) will be administered a day before the SMC drugs (AQ and SP) providing ample opportunity to objectively assess the tolerability of the different drug regimen.

The limitations of this study include the inability to mask the study drugs from parents and their children. Nevertheless, the use of control medications will ensure all study children receive equal number of medications and this could minimise bias due to unmasking. Also, the prevalence of malaria and STH is low in the study area and this may make it challenging to determine the effectiveness of the combined administration of SMC and anthelminthic drugs among the study participants but the study will provide important information on the safety and tolerability of administering SMC and antihelminthincs through a common delivery system. Measurement of efficacy is likely to require a larger study.

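### The protocol fixes an unmasked data analyst without giving a reason; coding the arms until the analysis is locked would reduce arm-aware choices at little cost

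*Protocol article*

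**What the plan says.** Who will be blinded {17a} separates the staff who give the drugs from those who assess safety and says of the latter: "This group of study staff who will perform the safety assessments will be blinded to the treatment arms". The next sentence deals with the analysis: "The data analyst will not be masked to the sources of the data". Procedure for unblinding if needed {17b} agrees: "The design is open label with only outcome assessors being blinded, so unblinding will not occur". The Discussion concedes the position of families: "The limitations of this study include the inability to mask the study drugs from parents and their children".

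The primary outcome depends on a causality judgement: "All solicited and unsolicited adverse events will be assessed for causal relationships to the study medications". Adverse event reporting and harms {22} gives that judgement to the investigators, who "will make determinations regarding the severity of the adverse events and their relation to a study drug".

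On analysis sets, section {20c} names an intention-to-treat analysis of all randomised children, a per-protocol analysis of those who complete four SMC cycles, and a full analysis set with this rule: "Participants who have only a pre- or post-intervention data will be excluded from the full analysis set". Section {31c} promises public access to the dataset and the statistical code.

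**The concern.** This is a decision that the article states, not a detail it leaves out. Families know what the children received, so knowledge of the arm may already colour what they report. The control supplements are meant to limit that, but they do nothing once the data reach the analyst. Masking the analyst is one of the few protections still available at that stage, and the article sets it aside without a reason.

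The trial's hoped-for result also has a direction: no more side effects in the combination arms, and less anaemia and infection. With the arms known, each open choice can be made in view of whether it helps or hurts that result, even without intent. Readers of the final report would have to take on trust that this did not happen.

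**Working it through.** The plan gives no figure on this point, so the check is mainly a reading of the sections side by side.

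**1. Meaning of the sentence.** The words about the sources of the data are loose. They stand under the blinding heading, directly after the statement on treatment arms, and {17b} limits blinding to outcome assessors. The reasonable reading is that the analyst knows the arms. No other section says that the arms are coded for analysis or that the analysis is locked before they are revealed.

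**2. Choices the text leaves open.**
- *Intensity of Plasmodium infection.* Secondary outcomes specifies an arithmetic mean. Statistical methods {20a} specifies a geometric mean of positive samples. The two can rank arms differently when counts are skewed.
- *Test for parasite counts and haemoglobin.* {20a} names a Student t-test at each time point and a repeated-measures analysis of variance across time points for the same outcomes. It does not say which carries the conclusion.
- *Analysis set.* {20c} names three sets and does not say which one leads for which outcome.

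**3. What the analyst does and does not decide.** Choosing among the options in step 2 falls to the analysis. Membership of each set is largely fixed by rule: randomised, completed four cycles, or both time points present. Severity and relatedness of adverse events belong to the investigators. Masking the analyst therefore bears on summary measures, tests and the choice of set. It does not by itself bear on event classification.

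**4. Scale, as illustration only.** A simulation was run under assumed inputs that are not in the documents, apart from the group size:
- no true effect, and two groups of 180 children (200 × 0.9, the planned enrolment less the 10% loss);
- baseline to follow-up correlation of 0.3, 0.5 or 0.7;
- 85% of children per protocol, at random;
- 10,000 repetitions for each correlation.

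Six haemoglobin analyses were formed: follow-up value, change, and baseline-adjusted value, each on all children and on per-protocol children. The error rate is the share of repetitions in which the smallest of the six p-values is below 0.05.

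| Correlation | One fixed analysis | Best of six |
|---|---|---|
| 0.3 | 4.96% | 11.8% |
| 0.5 | 5.05% | 13.1% |
| 0.7 | 4.96% | 13.6% |

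This is what wholly free selection could do. It does not predict this trial. Coding alone would not prevent it, because an analyst with arms A/B/C can still pick the smallest p-value. Coding hides the direction; locking sets and code removes the selection.

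**The case against.** The strongest reply is that the article is open and consistent: it claims blinding of observers only, and {17b} matches {17a}. Unmasked analysts are common in open-label trials. An analysis plan that is not shown may already fix summary measures, tests and leading sets, and public data and code allow later checking. All of this stands and limits the weight of the point. Later checking, however, can only detect an arm-aware choice; it does not prevent one.

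Three stronger readings are tempting, and the documents do not support them.
- A reader might infer that masking the analyst would protect the classification of adverse events. The text places severity and relatedness with the investigators, so an A/B/C dataset for the analyst alone would not reach those judgements.
- A reader might infer that the study pharmacist holds the allocation in a separate list, so that masking needs only one recoded variable. Sections {16a} and {16c} say only that the pharmacist generates the sequence and that research assistants assign the arms. Section {11c} adds a record of drug administration for each child. A key would have to be set up and the revealing fields withheld.
- A reader might wish to express the possible bias as a shift in the adverse-event rate. The article gives no expected rate and no number of disputable events, so any such figure would be invented.

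Masking would also be imperfect. Egg counts after treatment may partly reveal the praziquantel arms, and coding does nothing about caregiver reporting.

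**Conclusion.** The point holds in limited form and is minor. The article commits to an unmasked analyst, gives no reason, and describes no substitute safeguard at the analysis stage, while its own text leaves the choices in step 2 open. Coded arms combined with a lock before unmasking would reduce arm-aware choices without abolishing them.

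No size of bias follows from the documents. The change leaves sample size, alpha and power untouched. The conclusion assumes that the sentence refers to treatment arms and that no unseen plan already prescribes coding or a lock. If such a plan exists, the sentence in the article should be brought into line with it.

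**What to change.** Replace the sentence in {17a} with wording to this effect: *the analyst will work with arms coded A/B/C, under a key held by someone outside the analysis and with arm-revealing drug-administration fields withheld, until analysis sets, outcome derivations and analysis code are locked; the investigators' severity and relatedness judgements on adverse events will be finalised before the key is released.* If the team prefers not to mask, it should state the reason and lock the analysis code and leading sets in advance.

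The last clause prevents event judgements from being revised once results by arm are known. It does not mask investigators who already know the arms.

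The cost is small: recoding the arm, withholding the drug-administration fields and keeping a separate key.

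On timing, the article reports recruitment complete on 21 June 2022 and follow-up until 30 November 2022. When it was written, the end-of-season outcomes could still be analysed under code. For the six-day adverse-event data this cannot be told, since the investigators were to review and analyse data as they came in. The report should say which outcomes were analysed under code.
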